### Statistical analysis

The primary and secondary endpoint analyses will be conducted on an intention-to-treat basis. Baseline comparisons between the 2 arms of the study will be made using means or medians and proportions with 95% confidence intervals. All endpoints and analyses have been prospectively categorised as either primary or secondary. Differences in both primary and secondary endpoints between the 2 arms of the study will be tested independently at the 0.05 level of significance, using a one-way ANCOVA model that will include the baseline value of a given outcome in question as a covariate. No formal adjustments will be undertaken to constrain the overall type I error associated with the secondary analyses. Their purpose is to supplement evidence from the confirmatory primary analysis to help more fully characterise the treatment effect. Results from the secondary analyses will be interpreted in this context.

Additional exploratory analyses of the effects of stratification factors on the differences in both primary and secondary endpoints between the two arms of the study will be undertaken by either explicitly including these factors into the model (injury status) or by treating them as random effects in a random-effect regression model (study sites).

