### Design

A multi-centre, assessor-blinded, randomised controlled trial will be conducted. Experimental group participants will undertake an intensive 12-week programme of FES-assisted cycling, while control group participants will undertake a passive cycling programme over the same period. The trial will be conducted in four spinal units in Australia and New Zealand. Ethical approval has been obtained from the Human Research Ethics Committees at Austin Health in Melbourne (H2012/04476), Royal Perth Hospital in Perth (EC 2012/080), Princess Alexandra Hospital in Brisbane (HREC/12/QPAH/085) and the Multi-region Ethics Committee in New Zealand (MEC/12/02/020) and at the University of Melbourne (Trial Sponsor, HREC 1237599). Participants will be provided with information sheets and written informed consent will be obtained prior to recruitment and baseline assessment. See Table 1 for the schedule of enrolment, interventions, and assessments.

**Table 1 Tab1:** **Standard Protocol Items: Recommendations for Interventional Trials (SPIRIT) checklist: schedule of enrolment, interventions, and assessments**

	Enrolment	Allocation	Intervention	Post-intervention
TIMEPOINT	***-t*** _***1***_	0	12 weeks	12 weeks

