### Randomisation

Participants will be randomly assigned to either the experimental or control group with a 1:1 allocation as per a computer-generated randomisation schedule stratified by participating site and injury status (AIS) A/B or AIS C). The randomisation schedule will be under the control of a central randomisation unit, independent of the trial, located at Neuroscience Trials Australia in Melbourne. A participant will be considered to have entered the trial once his/her randomisation is revealed to the site coordinator.

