### Statistical analyses

#### Sample size

The power analysis is for a one-way fixed effects analysis of covariance (ANCOVA) with two levels that correspond to FES cycling and passive cycling arms of the study. This analysis includes baseline value of muscle CSA in the thigh and calf as a covariate, and uses the value of muscle CSA in the thigh and calf at week 12 as the primary outcome. Based on available pilot data [17], the participants in the passive cycling arm are likely to lose around 33% of the baseline muscle CSA (mean = 75, SD = 20) over a period of 12 weeks after SCI (measured using MRI). Assuming this loss could be contained to 10% by the proposed FES cycling intervention, thus resulting in mean changes of 25 (SD = 20) and 7.5 (SD = 20) for passive cycling and FES cycling respectively, the total sample size of 42 patients equally distributed between FES cycling and passive cycling arms will yield power of 0.8 to reject the null hypothesis at 0.05 level of significance. The ANCOVA is conservative (that is assuming no correlation between the baseline and follow-up measures) and non-directional (that is two-tailed) which means that an effect in either direction will be interpreted. Allowing for a15% drop-out rate, the final sample size for this study is calculated to be 50 patients equally distributed between FES cycling and passive cycling arms.

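### Allocation is stratified by site and AIS status, but the confirmatory ANCOVA omits both; if they are prognostic beyond baseline, the test is conservative and precision is given up

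*Protocol article*

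**What the plan says.** The Randomisation section of the protocol article allocates 1:1 from a "computer-generated randomisation schedule stratified by participating site and injury status (AIS) A/B or AIS C". The Design section gives four spinal units, so there are 4 × 2 = 8 strata.

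The Statistical analysis section tests primary and secondary endpoints "using a one-way ANCOVA model that will include the baseline value of a given outcome in question as a covariate". The Sample size section powers the same baseline-only model.

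Site and injury status come in only afterwards, under "Additional exploratory analyses of the effects of stratification factors on the differences in both primary and secondary endpoints". There, injury status is a model term and site is a random effect.

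**The concern.** Stratified allocation balances the arms within each site and AIS group. If those factors affect the outcome, the balancing removes their contribution from the true sampling variance of the arm difference. A model without them still counts that contribution as residual noise, so its standard error describes a less precise experiment than the one performed. Confidence intervals come out too wide and the rejection rate under the null falls below the nominal 0.05.

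At stake is precision in a small trial, with 42 evaluable participants planned and power close to 0.8. The protocol both fixes the confirmatory model and assigns the strata to a different tier, so this is a stated choice and not a detail left for a later document. The exploratory models do not repair it, because the confirmatory test remains the unadjusted one.

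**Working it through.** **Inputs from the documents.** Four sites (Design); AIS A/B versus C and 1:1 allocation (Randomisation); "mean changes of 25 (SD = 20) and 7.5 (SD = 20) for passive cycling and FES cycling respectively", two-sided 0.05, no baseline correlation, 42 evaluable, 15% drop-out (Sample size).

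**Inputs assumed.** R², the share of residual variance after baseline CSA that site and AIS explain, is taken from 0 to 0.30. Permuted blocks of 4 and an AIS C share of 25% or 30% are also assumed. The article gives none of these.

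**Step 1: reproduce the plan's figure.** The difference is 25 − 7.5 = 17.5 and the SD is 20.

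n per arm = 2 × (1.960 + 0.842)² × 20² / 17.5² = 20.5, rounded up to 21, or 42 in total. With drop-out, 42 / 0.85 = 49.4, so 50. Power at 21 per arm is 0.809 by the normal formula and 0.790 by the noncentral t with 42 − 3 = 39 df. The stated 42, 50 and 0.8 reproduce.

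**Step 2: power after adding the strata, by formula.** Four terms are added (3 for site, 1 for AIS), leaving 35 df. The residual SD becomes 20 × √(1 − R²), and the noncentrality is 17.5 / (residual SD × √(2/21)). For the planned model this is 17.5 / 6.17 = 2.84. At R² 0.20 the adjusted model has residual SD 17.9, standard error 5.52 and noncentrality 3.17.

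The formula assumes exact balance within strata. With about 42 / 8 ≈ 5 completers per stratum that will not hold, so simulation is the better guide.

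**Step 3: simulation.** 50 randomised, 42 completers, 8 strata, blocks of 4, 30% AIS C:

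| Assumed R² | Adjusted power, formula (planned 0.790) | Planned power, simulated | Adjusted power, simulated | Type I error of planned test, simulated |
|---|---|---|---|---|
| 0 | 0.787 | 0.78 | 0.76 | about 0.05 |
| 0.05 | 0.807 | 0.78 | 0.77 | about 0.05 |
| 0.10 | 0.828 | 0.78 | 0.80 | about 0.04 |
| 0.20 | 0.869 | 0.79 | 0.84 | about 0.03 |
| 0.30 | 0.909 | 0.80 | 0.89–0.90 | about 0.03 |

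**Step 4: the mechanism.** A second simulation used 42 participants without loss, 25% AIS C, R² split equally between site and AIS, and 6,000 runs per setting. Under no treatment effect it compares the planned model's mean standard error with the actual SD of its estimates:

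| Assumed R² | Mean SE, planned model | True SD of planned estimate | Ratio | Mean SE, adjusted model |
|---|---|---|---|---|
| 0 | 6.21 | 6.31 | 0.98 | 6.29 |
| 0.10 | 6.22 | 6.09 | 1.02 | 5.96 |
| 0.20 | 6.24 | 5.82 | 1.07 | 5.64 |
| 0.30 | 6.24 | 5.46 | 1.14 | 5.26 |

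The planned test's type I error was 0.053, 0.045, 0.034 and 0.022 down these rows; the adjusted test's ran from 0.046 to 0.057. Mean estimates were close to the true effect throughout (0 or 17.5), so there is no bias.

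**Step 5: what the R² values mean.** If AIS alone carries the effect and 30% are AIS C, the variance of the indicator is 0.3 × 0.7 = 0.21. The AIS difference needed is 20 × √(R²/0.21): 9.8 units at R² 0.05, 13.8 at 0.10, 19.5 at 0.20 and 23.9 at 0.30. If site shares the load, the AIS difference needed is smaller.

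**The case against.** The strongest reply is that the loss is conditional. It needs site or AIS status to predict week-12 CSA after baseline CSA is in the model, and the protocol gives no figure for that. A reader might infer that AIS C participants lose less muscle because they keep some motor function. That is plausible, and choosing AIS as a stratification factor suggests someone expected it to matter, but the documents do not state it. At R² 0.20 with AIS alone, the required 19.5-unit difference exceeds the planned treatment effect of 17.5. At R² 0.05 to 0.10 adjustment changes power by about −1 to +2 points. This objection stands: the size cannot be asserted.

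The second reply is that nothing planned is invalid. The sample size section sizes the trial for exactly this baseline-only ANCOVA, with SD 20 and no credit for covariates. Planned power stays at 0.78 to 0.80 in every setting tried. This also stands. A reader might infer that the trial falls short of its stated power, but what is forgone is extra precision.

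A reader might also infer that the plan leaves two competing treatment estimates. It does not: it names one confirmatory primary analysis and labels the stratum models exploratory. Likewise, random site effects appear only in those exploratory models, so they are no fault in the confirmatory test.

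None of this answers the core point. Allocation uses factors that the confirmatory model ignores, and including them costs little if they prove unimportant.

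**Conclusion.** The point holds as a conditional efficiency concern. Omitting the stratification factors makes the planned test conservative if they are prognostic beyond baseline CSA, and harmless if they are not. It causes no bias and no inflation of type I error, and the stated sample size and power stand.

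The size rests on an assumed R², assumed blocks of 4 and an assumed AIS C share. On those assumptions adjustment gains about 2 points of power at R² 0.10, about 5 at 0.20 and 9 to 10 at 0.30. It loses about 1 point at 0.05 and about 2 at 0. The trade is uneven: a small, bounded cost against a larger possible gain. It would be too strong to say outright that the standard error is too large or that the test runs below 5%; that is so only when the strata carry information that baseline CSA does not.

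**What to change.** In the Statistical analysis section, define the primary model as the week-12 value on arm, baseline value, AIS stratum (A/B versus C) and site, with AIS and site as fixed effects. Use the same form for the secondary endpoints. Keep the baseline-only ANCOVA as a sensitivity analysis, and keep stratum-by-arm interactions as exploratory. Fixed site effects are suggested because four sites give little information for estimating a between-site variance.

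The cost is a sentence or two of analysis wording and 4 degrees of freedom (39 to 35 at 42 completers), with up to about 2 points of power lost if the strata are not prognostic. Trial conduct and sample size do not change.

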### Data integrity and management

Data will be stored electronically on a database with secured and restricted access. Data transfer will be encrypted and any information capable of identifying individuals removed.

### Withdrawals

A participant will be considered to have withdrawn from the trial when consent is revoked or if the participant cannot be contacted or located. If this occurs, no further assessments will be performed. Participants will not be withdrawn from the trial for protocol violations.

### Monitoring

The trial will be overseen and monitored by a Programme Manager. The Programme Manager will visit each site to examine trial procedures, ensure data quality and monitor compliance with the trial protocol. All adverse events and serious adverse events will be recorded according to standard procedures. An interim safety analysis is planned when 25 participants have completed their post-intervention assessment. It will be done by an independent Data Safety Monitoring Board (DSMB) comprising a statistician and two rehabilitation doctors. If there are concerns about the safety of participants, this board will make a recommendation to the trial steering committee about continuing, stopping, or modifying the trial.

## Discussion

This trial will provide information about the relative effectiveness of FES-assisted cycling versus passive cycling in preventing muscle atrophy. This is important because muscle atrophy is associated with blood vessel atrophy [48] and predisposes to the development of pressure ulcers. The mechanisms by which active and passive exercise programmes improve function after SCI also need to be better understood because they allow for development of new and more effective therapeutic strategies. In this study, the control intervention is not standard care but an active intervention, involving passive cycling. This ensures that the intensity of both exercise programmes is similar, so that the effects of active exercise of the paralysed lower limbs can be identified over and above passive movement of the limbs.

This trial will adhere to key methodological principles important for minimising bias (International Conference on Harmonisation Good Clinical Practice annotated by the Therapeutic Goods Administration of Australia) [49] and will be reported according to the CONSORT guidelines [50]. For example, allocation will be concealed and randomised, assessors will be blinded and analyses will be performed on an intention-to-treat basis. Therapists and participants will not be blinded due to the nature of the intervention. One primary outcome and a number of secondary outcomes will be used. The primary outcome is a measure of muscle CSA. The secondary outcomes include measures of a biomarker for disuse osteoporosis, body composition, neurological function, and quality of life. Importantly, all adverse events will be rigorously documented, so that the safety of the interventions can be evaluated. It is anticipated that this trial will take 24 months to complete.

## Trial status

Recruitment commenced in October 2012. Recruitment continued until 31 May 2014.

## Abbreviations

AED: Anti-epileptic drugs
AIS: American Spinal Injuries Association Impairment Scale
ANCOVA: Analysis of covariance
AQoL-8: Assessment of Quality of Life 8
β-CTX: β-isomerised C-terminal telopeptide of collagen type I
BDNF: Brain derived neurotrophic factor
BMD: Bone mineral density
CCL2: Monocyte chemotactic protein-1(MCP-1)
CONSORT: Consolidated Standards of Reporting Trials
CSA: Cross-sectional area
CV: Coefficient of variation
CX3CL1: Fractalkine
DSMB: Data Safety Monitoring Board
ELISA: Enzyme-linked immunosorbent assay
FES: Functional electrical stimulation
FGF2: Fibroblast growth factor 2
HADS: Hospital Depression Anxiety Scale
HUI-3: Health Utilities Index Mark 3
IL: Interleukini
INF: Interferon
ISAK: International Society for the Advancement of Kinanthropometry
ISNCSCI: International Standard for Neurological Classification of Spinal Cord Injury
MRI: Magnetic Resonance imaging
P1NP: N-propeptide of type I procollagen
SD: Standard deviation
SCI: Spinal cord injury
SPIRIT: Standard Protocol Items: Recommendations for Interventional Trials
TNFα: Tumour necrosis factor alpha
VEGF: Vascular endothelial derived growth factor
WHOQoL-Bref: World Health Organisation Quality of Life Short Form
Wnt: Wingless-related integration site gene.
